### Outcome measures

#### Primary outcome measures

Difference in mean frequency of leakage over 24 hours based on a 72-hour diary (Additional file 3) compared with baseline. The mean frequency of leakage over a 24-hour period is calculated from the 72-hour voiding diaries, measured four times, in weeks 2, 4, 6 and 8. This mean frequency is compared with the baseline frequency measured at week 0.Difference in mean degrees of leakage over 24 hours based on a 72-hour diary, compared with the baseline. The mean quantity of fluid loss over a mean of 24 hours is calculated from the 72-hour voiding diary, measured three times, in weeks 2, 4, 6 and 8. This mean degree of leakage is compared with the baseline mean degree measured at week 0. The degree can be divided into four levels: mild degree (a very small amount of leakage with several drops); moderate degree (moderate leakage which wets the women’s underwear, but does not wet the over-trousers); and severe degree (a large amount of leakage which wet the over-trousers)A severity index for FSUI: frequency of leakage × amount of leakage, comparing the value of weeks 2, 4, 6 and 8 with baseline (0 week).

Scoring for frequency of leakage is defined as: 1 = less than once per month; 2 = several times per month; 3 = several times per week; 4 = every day or night.

Scoring for amount of leakage is defined as: 1 = a few drops; 2 = small splashes; 3 = more than small splashes.

Giving a severity index of: mild = 1–2; moderate = 3–6; severe = 8–9; very severe = 12. [15].

All of the primary outcome measures are based on a 72-hour diary. Every 2 weeks, patients will be asked to record the amount of fluid they drink (tea, coffee, milk, water and so forth) and leakage information (what movement they were doing when the leakage happened) for 3 consecutive days. Researchers will calculate the above primary outcome measures according to the patient’s record.

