**Methods/design:**

A randomized controlled trial has been designed to evaluate the therapeutic benefit of electroacupuncture for female stress urinary incontinence compared with pelvic floor muscle training. The safety of electroacupuncture and patient compliance will also be evaluated. Untoward reaction to the electroacupuncture, including a broken needle, fainting on acupuncture, or pain during acupuncture, will be recorded and the therapy will be stopped if an untoward reaction occurs. After we have received full ethical approval and patient consent, participants will be randomized to receive a series of 24 electroacupuncture or pelvic floor muscle training interventions. The frequency and amount of leakage will be measured as the primary outcome parameters. Secondary outcome parameters include the 1-hour pad test, the short-form of the International Consultation on Incontinence Questionnaire, patient subjective effectiveness evaluation, weekly usage of pad, and usage of specialty therapy for female stress urinary incontinence.

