**Trial design.**

In China, the prevalence of urinary incontinence in women is 46.5%, of which SUI makes up 59.6% [4]. Any women of old age are at high risk of SUI [5]. Women with SUI are embarrassed to take part in social activities, and as a result their lifestyles are altered putting them at increased risk of lifestyle-related disease, such as osteoporosis, obesity, diabetes, hypertension, coronary disease, mammary cancer, carcinoma of colon, depression, anxiety, and so forth [6].

The International Consultation on Urological Diseases recommend that treatment methods for mild and moderate SUI are lifestyle intervention, behavior therapy, pelvic floor muscle (PFM) training, functional electroacupuncture, and so forth [7]. PFM training has level A evidence of efficacy, with a curative rate ranging from 30 to 60% [8]. However, training duration should be at least 2 months. In China, PFM training is not as efficient as expected because there are not enough physical therapists, and patient compliance to treatment needs to be improved [9]. Primary therapy for moderate and severe SUI is surgery, which carries a high potential for adverse events. A safety communication from the US Food and Drug Administration on serious complications associated with transvaginal placement of a surgical mesh for pelvic organ prolapse was issued on 13 July 2011 [10]. Therefore, there is a need to explore other treatment avenues.

By contrast, acupuncture for FSUI works over a short period with a high curative rate [11], which shows potential advantages for FSUI. In a previous study [12], electroacupunture was verified as a more effective therapy for SUI than acupuncture, possibly related to the PFM and nerves. However, the level of evidence was rated as “low” [12].

A trial of high methodological quality is needed to determine whether electroacupuncture is effective for FSUI. This trial will evaluate the effect of electroacupuncture and investigate whether electroacupuncture is a better treatment for FSUI than PFM training.

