### Sample size

The sample size calculation was based on former study results [10]. In a previous study, the frequency of leakage using a mean 24-hour pad test in the electroacupuncture group was reduced 1.52 to 3.34 times (95% confidence intervals, and the frequency of leakage with a mean 24-hour pad test in the PFM training group was reduced 1.5 ± 1.1 times [16]. With 90% power and alpha = 0.05, and using anticipated drop-out rates of 20%, the required sample size was calculated as 320 overall.

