### Data analysis

The statistical analysis will be performed by a statistician blinded to allocation in the Clinical Evaluation Center of China Academy of Chinese Medical Sciences.

Statistical analyses will be performed using the SPSS statistical package program (ver.16.0; and the level of significance will be established at <0.05. The data analysis of baseline characteristics is based on the intention-to-treat population (data of all randomized participants will be analyzed).

The data analysis of the primary and secondary outcomes is mainly based on the intention-to-treat population. In addition, the data analysis of the primary outcome is also based on the per-protocol population as a supportive analysis. For primary and secondary outcome measures, analysis of covariance will be used to investigate whether electroacupuncture is more effective than PFM training.

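### Three unranked primary outcomes over four diary weeks, all tested at 0.05 with no deciding endpoint or success rule, leave the stated 5% error and 90% power describing only a single frequency comparison

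*Protocol article*

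**What the plan says.** All references are to the protocol article.

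- **Primary outcome measures.** Three outcomes are listed, and the section refers to them together as primary. Leakage frequency is taken from "72-hour voiding diaries, measured four times, in weeks 2, 4, 6 and 8". Degree of leakage comes from the same diary; its text gives a count of three measurements but lists the same four weeks, and I take the four listed. The severity index (frequency times amount) is defined by "comparing the value of weeks 2, 4, 6 and 8 with baseline (0 week"). No outcome is ranked first and no week is singled out.
- **Data analysis.** Analysis of covariance is used for every primary and secondary outcome, to show that electroacupuncture is the more effective treatment, and "the level of significance will be established at <0.05". The section gives no ordering of outcomes, no joint-success rule and no summary over weeks.
- **Sample size.** The calculation uses leakage frequency only, and "the required sample size was calculated as 320 overall". No week is named.
- **Discussion.** The sample size is said to secure 90% power for valid conclusions.
- **Abstract, Methods/design.** Two primary parameters are named: "The frequency and amount of leakage will be measured as the primary outcome parameters".

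**The concern.** The trial asks one confirmatory question: is electroacupuncture better than pelvic floor muscle training? The plan does not say which result answers it. An error rate of 5% and a power of 90% belong to a defined decision rule. The only rule that gives this pair is one comparison of leakage frequency, and the plan does not designate that comparison as decisive.

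Two consequences follow, depending on how success is later defined. If any significant primary result is enough, a false claim of superiority is more likely than 5%. If every primary outcome must be significant, the trial is less likely to succeed than the stated 90%. Leaving the choice open until results are known would also let the outcome and week be picked after the fact, and a reader could not tell whether that had happened.

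**Working it through.** **Inputs from the article.** Three primary outcomes; weeks 2, 4, 6 and 8; significance level 0.05; power 90%; drop-out 20%; 320 patients; 1:1 allocation. Sidedness is not stated, so two-sided is assumed. The correlations below are my assumptions, because the article gives none.

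**Step 1. The plan's own figure.** The electroacupuncture interval of 1.52 to 3.34 has midpoint 2.43, so the difference from 1.5 is 0.93. With the only stated SD, 1.1:

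n per arm = 2 × 1.1² × (1.960 + 1.282)² / 0.93² = 29.4, so 30 per arm and 76 in total after dividing by 0.8.

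This does not give 320. The electroacupuncture SD is not stated. If it is derived from the interval, 320 is reached when the earlier study had about 43 patients in that arm (SD 3.04, pooled SD 2.29, 128 per arm, 256 / 0.8 = 320). That number is not in the article, so 320 can be neither confirmed nor called wrong. The rest of this check does not depend on it.

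**Step 2. How many tests.** If the four diaries are averaged for each outcome: 3 × 1 = 3. If each week is tested: 3 × 4 = 12.

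**Step 3. Error rate if any one significant result counts.** With independent tests:

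- 3 tests: 1 − 0.95³ = 0.143
- 12 tests: 1 − 0.95¹² = 0.460

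The outcomes share the same diaries, and the index is built from frequency and amount, so positive correlation is expected. I simulated 400,000 sets of correlated z-statistics with no treatment effect. Between-outcome and between-week correlations multiply for pairs that differ in both.

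| Between outcomes | Between weeks | 3 tests, any p<0.05 | 12 tests, any p<0.05 | 12 tests, any favouring electroacupuncture |
|---|---|---|---|---|
| 0.3 | 0.5 | 13.5% | 38.3% | 19.9% |
| 0.5 | 0.7 | 12.5% | 30.3% | 15.4% |
| 0.7 | 0.7 | 11.0% | 26.6% | 13.3% |
| 0.9 | 0.9 | 8.4% | 15.0% | 7.5% |

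The between-week correlation does not enter the 3-test column. The reference for the last column is 2.5%, half of a two-sided 5%. Every scenario exceeds its reference value.

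**Step 4. Chance of success, if each outcome alone has 90% power.** This is generous to degree and severity index, for which no power is given.

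- All three must be significant: 0.9³ = 0.729 if independent, rising to about 0.85 at correlation 0.9. The false-positive rate for this joint claim does not exceed 5%.
- Any one of three is enough: about 94% (correlation 0.9) to 99.9% (independent), with the error rates of step 3.

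Neither rule yields 5% error together with 90% power. One outcome at one week yields both, by construction.

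**The case against.** Several objections have weight.

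- **The count of 12 is a reading.** For frequency and degree the text goes on to speak of one mean set against baseline, which may be a single average over four diaries. The severity-index wording points more to separate weeks. Where the article wants averaging in the Secondary outcome measures, it gives explicit divisors, and the primary outcomes have none. The text does not settle it, so 12 tests and the 46% figure must not be presented as what the plan does.
- **No any-win rule is stated.** A reader might infer that any single result could carry the claim. The article does not say so; the defect is that it gives no rule.
- **Power.** A reader might infer that the trial is underpowered because alpha must be divided over the outcomes. The plan proposes no such division and the remedy needs none, so that power loss is not a property of this plan.
- **Timing.** The Background says of pelvic floor muscle training: "However, training duration should be at least 2 months". A reader might conclude that weeks 2, 4 and 6 are invalid for the comparator. The article does not say that earlier assessment is unfair, and it presents a short time to effect as a possible advantage of acupuncture. The sentence supports week 8 as the deciding visit and shows no separate error.
- **Abstract.** Naming two parameters when the third is their product may be condensation. It is a minor inconsistency.
- **Unseen analysis plan.** Adjustment mechanics may sit there. Which outcome and week are primary belongs in the protocol, and this text does address it, by listing three outcomes over four weeks.

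What stands is that even on the most lenient reading, three averaged outcomes, three unranked tests at 0.05 remain.

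**Conclusion.** The point holds in this form: the article fixes three primary outcomes over four weeks without a lead outcome, deciding week or success rule, and tests them all at 0.05. If any one win counts, the false-positive chance is about 8–14% for 3 tests. For 12 tests it is about 15–38%, with 46% only if they were independent, which is implausible here. If all three outcomes are required, error is controlled and the chance of success is about 73–85%. The 5% and 90% given under Sample size and repeated in the Discussion therefore describe one frequency comparison and not the superiority claim as the plan leaves it.

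These sizes rest on two-sided testing, on assumed correlations of 0.3–0.9 between outcomes and 0.5–0.9 between weeks, and, for the chance of success, on 90% power for each outcome. That 5% is exceeded under an any-win rule does not depend on the exact correlations within those ranges.

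**What to change.** Before unblinding:

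1. Designate one primary endpoint: change from baseline in mean 24-hour leakage frequency, from the 72-hour diary, at week 8. Test it with the planned analysis of covariance, with baseline as covariate, at 0.05. Frequency is the kind of outcome the trial was sized on, although the Sample size section names no week and refers to a pad test instead of the diary; that wording should be reconciled. Week 8 is the end of both treatment courses.
2. Make degree of leakage, the severity index and weeks 2, 4 and 6 secondary. Either test them in a stated fixed order after the primary or report them with confidence intervals only.
3. Bring the Abstract into line.

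This keeps alpha at 0.05, the planned power for the primary comparison and 320 patients, and adds no visits. The cost is fewer routes to a positive claim. Because the Trial status section says the study started on 1 March 2014 and the trial is registered, the change needs a dated amendment and a registry update, with a statement that it was made before unblinding.

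### The severity index, a primary outcome, cannot be derived from the 72-hour diary that is its stated source, and neither it nor the degree scale states a value for a woman who does not leak

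*Protocol article*

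**What the plan says.** The section on primary outcome measures in the protocol article lists three outcomes: mean 24-hour frequency of leakage, mean degree of leakage, and a severity index. Each is compared with week 0 at weeks 2, 4, 6 and 8.

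- **Source.** "All of the primary outcome measures are based on a 72-hour diary". Every two weeks the woman records fluid intake and "leakage information (what movement they were doing when the leakage happened) for 3 consecutive days". The scoring is then done from that material: "Researchers will calculate the above primary outcome measures according to the patient’s record". No separate weekly or monthly recall question is mentioned.
- **Index, frequency factor.** "1 = less than once per month; 2 = several times per month; 3 = several times per week", and a top score of 4 for leakage on every day or night.
- **Index, amount factor.** "1 = a few drops; 2 = small splashes; 3 = more than small splashes".
- **Index bands.** Products of 1–2 are called mild, 3–6 moderate, 8–9 severe and 12 very severe.
- **Degree.** "The degree can be divided into four levels: mild degree (a very small amount of leakage with several drops", followed by a moderate and a severe level. The list ends there, without a fourth level and without numeric codes.

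**The concern.** An index whose frequency categories refer to a week or a month is to be scored from three days. If the record cannot distinguish the categories, whoever scores it must guess or apply a rule that the article does not give, and the result depends on that rule.

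Both ends of the scale are also a problem. At the bottom, a woman who has become dry, the best possible response, has no value of her own. At the top, the daily category is open-ended, so improvement among women who still leak every day does not change the frequency factor. The Data analysis section plans analysis of covariance, mainly on all randomised women, so each woman with a diary needs a defined value for each primary outcome. The undefined fourth degree level leaves a smaller gap of the same kind.

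**Working it through.** **1. The stated bands.** Multiplying frequency scores 1–4 by amount scores 1–3 gives 1, 2, 3, 4, 6, 8, 9 and 12. The four printed bands cover exactly these values, so the scale is internally consistent. Its minimum is 1 × 1 = 1, which falls in the mild band. No product is 0 and no band means dry.

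**2. What three days can show.** The article gives no leak rates, so the rates here are assumed. With Poisson leaks, P(empty diary) = exp(−3 × leaks per day), taking a month as 30 days.

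| Assumed true rate | Frequency score by definition | P(empty 72-hour diary) |
|---|---|---|
| 0.5 per month | 1 | exp(−0.05) = 0.95 |
| 2 per month | 2 | exp(−0.20) = 0.82 |
| 4 per month | 2 | exp(−0.40) = 0.67 |
| 2 per week | 3 | exp(−0.857) = 0.42 |
| 3 per week | 3 | exp(−1.286) = 0.28 |
| 1 per day | 4 | exp(−3) = 0.05 |
| 1.5 per day | 4 | exp(−4.5) = 0.01 |

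An empty diary is therefore compatible with scores 1, 2 and 3, and with cure. Even if the amount were set to its lowest score of 1, the index could be 1, 2 or 3, which spans mild and moderate.

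A diary with one leak is no clearer. If that leak has the largest amount, reading it as several a month gives 2 × 3 = 6 (moderate), and reading it as several a week gives 3 × 3 = 9 (severe).

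**3. The top category.** The Sample size section plans on a mean reduction of 1.5 with pelvic floor muscle training and of 1.52 to 3.34 with electroacupuncture, midpoint (1.52 + 3.34)/2 = 2.43. I read these as leaks per 24 hours. A mean reduction cannot exceed the mean at baseline, so the planning figures imply a mean baseline of at least 1.5 to 2.43 leaks a day, in or near the daily category. By the scale's definition, a woman who goes from 4 leaks a day to 1 has frequency score 4 both times.

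In practice the score depends on the missing scoring rule. If score 4 required a leak on all three diary days, a woman averaging 1 leak a day would meet it with probability (1 − exp(−1))³ = 0.25.

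**4. The degree scale.** Four levels are announced and three are defined, each describing some leakage. A woman who leaks can be graded from her record. A woman with a leak-free diary has no stated degree.

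**5. Mean 24-hour frequency.** This is a count over three days divided by 3, and 0 is a natural value. It is not affected.

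**The case against.** A reader might infer that two of the three primary outcomes cannot be scored at all. For degree the text does not support this: recorded leaks can be graded, and the unprinted fourth level may be none or may be a higher grade. The diary form (Additional file 3) is not shown and could settle it. The degree outcome is also described as a quantity of fluid loss, for which zero is natural, and a coding rule for dry diaries could sit in an analysis plan. What stands is that the printed text contradicts itself, four levels against three, and states no degree for a leak-free diary.

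The form cannot rescue the index in the same way, because no form lengthens a 72-hour window. If it did carry a longer recall question, the article's statement of the source would be wrong. A month's recall at week 2 would also reach back before treatment.

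It is also tempting to say that a third or more of women would have no degree, because the Background credits pelvic floor muscle training "with a curative rate ranging from 30 to 60" percent. That text does not define cure, covers one arm only, and is not tied to a leak-free diary, so it gives no dry-diary rate. Nor do the documents say that dry women would be left out; the analysis is mainly by intention to treat. They do not support a stated direction or size of bias in the treatment comparison.

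Two further points limit the reach. If most women leak daily at baseline, empty diaries are rare then (about 1% at 1.5 a day), so misclassification at the low end matters mainly for strong responders. And a fall from 4 leaks a day to 1 is fully captured by mean 24-hour frequency, while the index can still move through its amount factor. Both points limit the damage to the trial, but neither makes the index derivable.

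**Conclusion.** The point holds for the severity index. The stated source cannot yield the stated score, because three diary days do not distinguish the lower three frequency categories. The index has no value for a dry woman, and its frequency factor is blind to change within daily leakage. The mismatch and the floor can be read directly from the text and rest on no assumption. The empty-diary probabilities of 0.67, 0.42 and 0.28 illustrate the mismatch under assumed Poisson rates. The implied baseline level rests on reading the planning reductions as leaks per 24 hours.

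For mean degree the defect is narrower: an undefined fourth level and no stated value for a leak-free diary. Mean 24-hour frequency, the measure on which the sample size is argued, stands. No corrected effect size or sample size follows from this point.

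**What to change.** Before unblinding, and in writing:

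1. Drop the severity index as a primary outcome or demote it to secondary. If it is kept as secondary, ask its frequency and amount items directly over a recall period that matches the categories, and only for women in whom a baseline can still be obtained.
2. Keep mean 24-hour frequency as primary.
3. List and code all four degree levels, with 0 = no leakage assigned to a leak-free diary, so that every randomised woman with a diary has a value. This repairs the degree outcome without replacing it.

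The cost is a change of wording, and at most two recall questions at existing visits. The downside is one fewer primary outcome. The Trial status section gives a start of 1 March 2014, so baseline recall cannot be recovered for women already enrolled, and the index would be unavailable or only partly available for them. Dropping or demoting it is therefore the practical route.

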### Secondary outcome measures

Difference in 1-hour pad test, compared with baseline. The quantity of fluid loss will be measured by 1-hour pad test, comparing the value at 8, 20 and 32 weeks with the baseline (0 week); values at 20 weeks are calculated from the total quantity of fluid loss over weeks 17 to 20 divided by 4; values at 32 weeks are calculated from the total quantity of fluid loss over weeks 29 to 32 divided by 4.The International Consultation on Incontinence Questionnaire-Short Form (Additional file 4) is a brief instrument used to assess the impact of urinary incontinence on patients’ lives. This is evaluated at 8, 20 and 32 weeks; values at 8 weeks are calculated by the total score at weeks 6 and 8 divided by 2.Patient subjective effectiveness evaluation uses three-point scoring: no help = 0; small help = 1; medium help = 2; great help = 3. This is evaluated at 8, 20 and 32 weeks; values at 8 weeks are made by the patient subjective effectiveness evaluation at week 8. If the 8-week value is not available, week 4 or week 6 can be used as the value at week 8.Weekly usage of pad. The value at week 8 is the average weekly usage of pads during weeks 1 to 8; the value at week 20 is the average weekly usage of pads during weeks 9 to 20; the value at week 32 is the average weekly usage of pads during weeks 21 to 32.Use of specialty therapy (surgery, medicine or other treatment except electroacupuncture and PFM training) for simple FSUI. The difference of use of specialty therapy for simple FSUI will be compared between the two groups during weeks 1 to 8, 9 to 20 and 21 to 32.Subgroup analysis: the amount of leakage with the 1-hour pad test as a measure of the curative effect of electroacupuncture for different extents of simple FSUI. Time point: 8, 20 and 32 weeks.

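### A missing week-8 subjective rating may be replaced by week 4 or week 6 in no fixed order, and fixed divisors for the pad test and ICIQ-SF do not say what happens when an assessment is missed

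*Protocol article*

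**What the plan says.** All the rules at issue are in the protocol article, Secondary outcome measures.

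- **Subjective effectiveness rating (0 to 3, higher is better).** Schedule and source of the week-8 value: "This is evaluated at 8, 20 and 32 weeks; values at 8 weeks are made by the patient subjective effectiveness evaluation at week 8". Replacement rule: "If the 8-week value is not available, week 4 or week 6 can be used as the value at week 8".
- **1-hour pad test.** Week 20: "values at 20 weeks are calculated from the total quantity of fluid loss over weeks 17 to 20 divided by 4". Week 32: "values at 32 weeks are calculated from the total quantity of fluid loss over weeks 29 to 32 divided by 4".
- **ICIQ-SF (short-form incontinence questionnaire).** Week 8: "values at 8 weeks are calculated by the total score at weeks 6 and 8 divided by 2".

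The section sets no minimum number of assessments for the averaged values and does not say how an incomplete set is handled.

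Two other sections bear on this. The Background states that PFM training should last two months or more, and contrasts it with acupuncture, which it describes as working over a short time. Data analysis bases the outcome analyses mainly on the intention-to-treat population, explained as "data of all randomized participants will be analyzed". The Sample size section allows for 20% drop-out, so absent values are foreseen.

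**The concern.** The replacement rule is a stated missing-data method, not a detail left for later. It has three weaknesses.

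1. Two source weeks are allowed and nothing decides between them, so two analysts following the text can obtain different week-8 values from the same records.
2. Weeks 4 and 6 are not among the listed rating times, so it is unclear whether such ratings will exist for every woman.
3. A mid-treatment rating stands in for an end-of-treatment one. On the protocol's own account of how fast each treatment acts, that costs the control more than electroacupuncture, in a trial that asks whether electroacupuncture is better.

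The fixed divisors raise a smaller, conditional issue. Lower pad-test and ICIQ-SF values are better. If an incomplete total is still divided by the full number, missed assessments look like improvement.

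**Working it through.** The plan states no figure for this point, so there is none to reproduce.

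**1. Replacement rating: timing**

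Both arms have three sessions a week for 8 weeks, 24 in all (Design; Interventions).

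- By the end of week 4: 4 × 3 = 12 sessions, 12/24 = 50% of the course.
- By the end of week 6: 6 × 3 = 18 sessions, 18/24 = 75% of the course.

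Eight weeks is itself only about the minimum duration that the Background gives for PFM training. Weeks 4 and 6 fall short of it. No such minimum is given for electroacupuncture.

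**2. Replacement rating: possible size**

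Let f be the share of an arm whose week-8 rating is replaced, and g the mean amount by which the replacement falls below the rating she would have given at week 8. The electroacupuncture-minus-PFM difference then shifts by

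f(PFM) × g(PFM) − f(EA) × g(EA).

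The protocol gives neither f nor g. For illustration I assume f = 0.20 in both arms, borrowed from the drop-out allowance. This is probably generous, since women who leave before week 4 have nothing to carry forward.

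| g(PFM), assumed | g(EA), assumed | Shift on the 0–3 scale |
|---|---|---|
| 1 | 0 | 0.20 × 1 − 0 = 0.20 |
| 0.5 | 0 | 0.20 × 0.5 − 0 = 0.10 |
| 0.5 | 0.5 | 0.10 − 0.10 = 0 |

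A positive shift favours electroacupuncture. The bias needs unequal g or unequal f.

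The lack of order matters whatever the bias. A woman rated 1 at week 4 and 2 at week 6 (assumed) may correctly be entered as either 1 or 2.

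**3. Fixed divisors, if applied as written to incomplete data**

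For a constant true loss L with m of 4 tests missed, the literal value is L × (4 − m)/4. Dividing by the number done gives L × (4 − m)/(4 − m) = L. With L = 10 g (assumed):

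| Tests missed | Total ÷ 4 | Total ÷ number done |
|---|---|---|
| 0 | 10 g | 10 g |
| 1 | 7.5 g | 10 g |
| 2 | 5 g | 10 g |
| 3 | 2.5 g | 10 g |
| 4 | 0 g | missing |

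For ICIQ-SF with one of two visits missed and a constant score of 10 (assumed): 10/2 = 5 literally, against 10/1 = 10 over the visits attended.

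Between arms, with no true difference, a mean of 10 g and an assumed chance p of missing each test, the literal mean is 10 × (1 − p):

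| Missing rates, arm A and arm B (assumed) | Literal means | Spurious difference |
|---|---|---|
| 20%, 20% | 8 g, 8 g | 0 |
| 10%, 20% | 9 g, 8 g | 1.0 g |
| 10%, 30% | 9 g, 7 g | 2.0 g |
| 0%, 20% | 10 g, 8 g | 2.0 g |

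If an incomplete set is instead made missing, this downward bias does not arise.

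**The case against.** **On the replacement rule.** It covers one secondary outcome, and only women without a week-8 rating. It applies to both arms. The statistician is blinded to allocation (Data analysis), so the choice of week could not knowingly favour an arm. All of this stands, and a reader should not infer that the rule invites deliberate selection. But blinding does not make an unordered rule reproducible, and equal application does not remove bias when the protocol itself expects the treatments to act at different speeds.

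**On the divisors.** A reader might infer that missed assessments are scored as zero. The text does not say so. With complete data the formulas are plain means, the same section calls an absent rating unavailable rather than zero, and an analysis plan that is not shown may set incomplete values to missing. The planned 20% is also drop-out rather than intermittent missed tests: a woman who leaves before week 17 has no test in the window, so the 25%-per-test figure does not describe her. What stands is that the wording, followed literally, gives a wrong value for an incomplete set.

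**Two further inferences fail.**

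- A reader might object that the pad-test series mixes single tests with four-week means. The section does not say how many tests are done at weeks 0 and 8. Any such definition applies equally to both arms, and averaging reduces noise.
- A reader might object that averaging ICIQ-SF over weeks 6 and 8 dilutes the week-8 effect. That is a pre-stated summary applied alike to both arms. Any figure for dilution would need an assumed course of improvement that the documents do not give.

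**Conclusion.** The replacement rule should be changed. It is explicit, it is not reproducible, it draws on weeks outside the stated rating schedule, and on the protocol's own premises it can bias the week-8 subjective comparison against PFM training. The direction rests on the Background's statements about speed of action. The size cannot be derived from the documents; under the illustrative assumptions it runs from 0 to 0.20 points on a 0–3 scale.

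The divisor wording needs clarifying, as a conditional point only. If it is applied as written to incomplete data, the pad-test value falls by 25% per missed test and the ICIQ-SF value by about half, for a constant true level. A between-arm bias would further require unequal missingness, on which the protocol is silent.

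The scope is narrow: the subjective rating at week 8, the pad test at weeks 20 and 32, and ICIQ-SF at week 8. No primary outcome is touched.

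**What to change.** 1. **Subjective rating.** Remove the replacement from the main analysis and treat an absent week-8 rating as missing. If ratings at weeks 4 and 6 are in fact collected, use them only in a sensitivity analysis with a fixed order, week 6 before week 4.
2. **Pad test at weeks 20 and 32, ICIQ-SF at week 8.** Define the value as the total divided by the number of assessments done, and as missing if none was done. The averaging windows can stay as they are.

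Both are changes of wording and need no new data collection, which matters because the trial started in March 2014. The costs are some missing week-8 ratings, and noisier averages for women with fewer assessments.
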